#### Secondary endpoints

The analysis of the secondary endpoints will be performed exploratory. The hypothesis

H03:·PXNon−Video>XStandard=12versusH12:·PXNon−video>XStandard≠12

will be tested using the exact *U*-test according to Mann and Whitney at the significance level α = 0.05. The change scores of the BBT, MAL, SIS, FAT, MRS, and BI as well as the WMFT and mortality between groups at all time points will be tested pairwise using the exact *U*-test according to Mann and Whitney and Chi-squared test respectively at the significance level α = 0.05. The effect measures will be the difference of medians with 95% confidence interval (Hodges-Lehmann) and the difference of proportions with 95% confidence interval (independent samples), respectively. Furthermore, the difference between end of training and 6 month after the training will be investigated within each treatment group concerning the BBT, MAL, SIS, FAT, MRS, and the BI as well as the WMFT scores. Therefore, 95% confidence intervals are computed for these differences (paired samples).

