### Sample size

The calculation of the sample size is based on the aim to detect a difference of 2.5 points in the WMFT
[16] between the videotherapy- and the standard group concerning the change from baseline until the end of rehabilitation, corresponding to δ = 0.5, with a power of 90% in the final of two analyses. The critical difference of 2.5 points in the WMFT
[16] results from our pilot study
[10-13]. Allowing for a maximal drop out of 20% of the patients, 125 patients need to be included in the study for each group, rendering a total sample size of 375 (α_2_(1) = 0.035, Mann–Whitney test).

The interim analysis is conducted according to Wang and Tsiatis
[34], after half of the patients in each group (63 in each group, a total of 188) have concluded the rehabilitation program. If the effect is considerably greater than assumed (δ = 0.7, corresponding to a difference of 3.5 change points), there is a probability of 80% to detect this at this early stage and hence to terminate the study early.

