#### Primary endpoint

The score difference cannot be assumed to be normally distributed, so that distributions will be compared by analyzing the probability that an observed change score X_Videotherapy_ in the videotherapy population is greater than an observation in the non-video X_Non-video_ or the standard population X_Standard_:

H01:·PXVideotherapy>XStandard=12versusH11:·P(XVideotherapy>XStandard)≠12

and

H02:·PXVideotherapy>XNon−video=12versusH12:·P(XVideotherapy>XNon−video)≠12

The comparisons will be performed in a hierarchical manner according to a suggestion by Wiens
[36,37]. For this procedure, the total significance level α is split into one portion for the first hypothesis α(1) and one for the second hypothesis α(2) = α – α(1). Accordingly, as we expect a major difference between the novel video-based rehabilitation and the standard physiotherapeutic rehabilitation, this difference will be tested first at the significance level α(1). If the null hypothesis can be rejected, we will secondly test the difference between videotherapy and non-video at the full significance level α. However, if the first hypothesis cannot be rejected, the second hypothesis can still be tested at the significance level α(2). The hypotheses will be tested using the exact *U*-test according to Mann and Whitney, and the specific significance levels are fixed using a sequential analysis plan (see Table
3).

**Table 3 T3:** Procedure of statistical analysis

**Analysis i**	**Time point**	**Hypothesis**	**Nominal level α**_**i**_	**Detectable effect δ**_**i**_	**Power**
1	Interim analysis	Video vs. standard	0.01	0.7	80%
		Video vs. non-video	0.01	0.7	80%
2	Final analysis	Video vs. standard	0.035	0.5	90%
		Video vs. non-video	0.01 or 0.045	0.47 or 0.55	90%

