#### Interim analyses

After half of the patients have concluded the rehabilitation program, an interim analysis will be performed. This will allow for an early termination of the study if the effects are greater than assumed for sample size determination while keeping an overall significance level of α = 0.05. The interim analysis is planned according to the designs suggested by Wang and Tsiatis
[34] and yields a nominal significance level of α1 = 0.01 for the interim analysis. At this time point, all three null hypotheses regarding the primary endpoint as stated above are tested at the full nominal significance level, and the study is terminated only if all null hypotheses are rejected.

For the final analysis, the three hypotheses of the primary endpoint are tested at a nominal significance level of α2 = 0.045 in the hierarchical manner described above. Specifically, the first hypothesis is tested at a significance level of α2(1) = 0.035. If this null hypothesis is not rejected, the second null hypothesis is tested at the remaining significance level of α2(2) = 0.01. However, if the first null hypothesis is rejected, the second is tested at the full nominal significance level of α2 = 0.045.

This procedure renders the following effects detectable in the different stages, as presented in Table
3. The effects are measured by the differences of medians, for which 95% confidence intervals (Hodges-Lehmann) are computed for both group comparisons.

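### On coarse secondary scales (FAT, MRS) the only planned effect measure may often read 0 beside a significant U-test; a tie-adjusted probability should be reported with it

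*Protocol article*

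**What the plan says.** Under Statistical analysis, Secondary endpoints, the protocol article lists the scores to be compared pairwise: "The change scores of the BBT, MAL, SIS, FAT, MRS, and BI as well as the WMFT and mortality between groups at all time points". The test is the exact Mann-Whitney U-test at two-sided 0.05. The effect measure follows directly: "The effect measures will be the difference of medians with 95% confidence interval (Hodges-Lehmann"). A difference of proportions is named as well, and read with the paired tests (U-test, Chi-squared) it belongs to mortality. No other measure is named for any scale, fine or coarse.

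The same section gives the status of these analyses: "The analysis of the secondary endpoints will be performed exploratory". The article states neither the number of grades of FAT or MRS nor how their change scores are distributed.

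**The concern.** The Hodges-Lehmann estimate is the median of all between-arm pairwise differences. On whole-number change scores every such difference is a whole number, so the estimate and both limits normally fall on whole numbers. The U-test works differently: it responds to the imbalance between pairs favouring one arm and pairs favouring the other, however many pairs are tied. On a scale where most patients change by 0 or 1 grade, the test can therefore reject while its companion estimate stays at 0.

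A line such as p < 0.05, difference 0 (95% CI 0 to 0) reads as a precisely measured absence of effect, when in fact more patients improved in one arm. In an exploratory analysis the estimate and its interval are the main output, so this is where the loss falls.

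**Working it through.** **Inputs.** From the article: 125 patients per group, at most 20% drop-out, Mann-Whitney test, two-sided 0.05 for secondary scores, mean imputation in the intention-to-treat set. Assumed: whole-number change scores with the distributions shown below.

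**1. The plan's own sample size.** The Sample size section sets the target as "corresponding to δ = 0.5, with a power of 90% in the final of two analyses", and Interim analyses states that "the first hypothesis is tested at a significance level of α2(1) = 0.035". With P(X>Y) = Φ(0.5/√2) = 0.638, Noether's formula gives a two-group total of (2.108 + 1.282)² / [12 × 0.25 × (0.638 − 0.5)²] ≈ 200.7. That is 100.3 per group, and 100.3/0.8 = 125.4. The stated 125 is reproduced, so about 100 complete cases per arm is the right basis.

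**2. When the estimate and limits stay at 0.** With 100 per arm there are 10,000 pairs.
- The estimate is 0 when fewer than half of the pairs favour either arm.
- The lower 95% limit is the ordered difference at about 5,000 − 1.96 × √(10,000 × 201/12) = 5,000 − 802 = 4,198, a share of 0.42. The interval is therefore [0, 0] when P(X>Y) and P(X<Y) are both below about 0.42. At 125 per arm the bound is 0.43.

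**3. One case in full.** Changes of (−1, 0, 1, 2) have probabilities (.05, .65, .28, .02) in the control arm and (.05, .45, .45, .05) in the video arm, so 30% versus 50% improve.
- P(X>Y) = .45×.05 + .45×.70 + .05×.98 = 0.387.
- P(X<Y) = .05×.95 + .45×.30 + .45×.02 = 0.192. Ties make up the remaining 0.42.
- Both shares are below 0.42, so at the expected values Hodges-Lehmann gives 0 with interval [0, 0].
- The U-test at the same values: P(X>Y) + ½P(X=Y) = 0.5 + (0.387 − 0.192)/2 = 0.598. The pooled shares are .05, .55, .365, .035, so the tie factor is 1 − Σ(share³) = 0.785. The null SE is √(201/120,000 × 0.785) = 0.0363, and z = 0.0975/0.0363 = 2.69, with p about 0.007.

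**4. Three moderate scenarios, simulated.** These are the case above, (.05,.60,.30,.05) versus (.03,.45,.45,.07), and (.05,.50,.38,.07) versus (.03,.37,.48,.12), so 30-45% of controls and 50-60% of video patients improve. Power was about 62-78%. Among significant results the estimate was 0 in about 98-100%, the interval included 0 in all, and it was exactly [0, 0] in about 57-74%.

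**5. Dependence on the assumed distribution.** Significant results only, 100 complete cases per arm:

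| Change scores | Estimate 0 | Interval [0, 0] |
|---|---|---|
| 15% vs 30% improving | 100% | 100% |
| 20% vs 40% | 100% | 93% |
| 30% vs 50% | 99% | 72% |
| 40% vs 60% | 97% | 44% |
| 20% vs 60% | 35% | 2% |
| 20% vs 70% | 1% | 0% |
| Rounded normal, 0.5 SD shift, SD 0.5 point | 100% | about 78% |
| same, SD 0.7 | about 90% | about 21% |
| same, SD 1 | about 43% | 0% |
| same, SD 1.3 | about 16% | 0% |
| same, SD 1.7 or more | at most 1% | 0% |

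An interval that still includes 0 beside p < 0.05 persists longer: 92% at 20% vs 60%, 97-98% at SD 1, 86% at SD 1.3 and 67-70% at SD 1.7. It falls to 30% at 20% vs 70%.

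**6. With mean imputation.** Adding 25 imputed values per arm to the three scenarios of step 4, the estimate is 0 in about 68-93% of significant results, [0, 0] occurs in about 0-22%, and the interval includes 0 in at least 98%. The arm mean gives the low ends for the zero estimate and for [0, 0]; the overall mean gives the high ends.

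**7. The tie-adjusted probability on the same data.** Expected value and approximate 95% CI at 100 per arm: 15% vs 30%, 0.571 (0.509-0.633); 20% vs 40%, 0.596 (0.530-0.662); 30% vs 50%, 0.598 (0.528-0.667); 40% vs 60%, 0.603 (0.532-0.674). Each excludes 0.5, where Hodges-Lehmann gives 0.

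**The case against.** **The inputs are not in the document.** This stands. Neither the grades nor the change distributions of FAT and MRS are given. A reader might infer that Hodges-Lehmann cannot show an effect on these scales, or that 0 is certain to be reported. The table does not support that: large effects or a change SD of about 1 point or more often give an estimate of 1.

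**The pilot points to a large FAT effect.** The Background reports p < 0.001 for FAT with 8 versus 8 patients. Without ties, an exact two-sided test needs U ≤ 2 for that (2 × 4/12,870 = 0.0006, against 2 × 7/12,870 = 0.0011 at U ≤ 3), so a probability of superiority of at least 62/64 = 0.97. An effect of that size would not leave the estimate at 0. But the pilot was very small and in chronic patients, and this trial is sized on its primary score for δ = 0.5, a probability of 0.638. Moderate effects are therefore a fair planning case.

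**Mean imputation breaks up the ties.** This stands in part. If it covers secondary endpoints, which the article does not say expressly, [0, 0] becomes uncommon, and a reader should not infer that it is the usual outcome under the full plan. The zero estimate remains in most significant results in the three scenarios, and any escape from it comes from imputed values.

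**The hypotheses are written with P(X>Y) = ½.** A reader might infer that the tested target is wrong for FAT and MRS. That notation ("distributions will be compared by analyzing the probability that an observed change score") is written for the primary comparisons and reused for the non-video versus standard hypothesis, where no scale is named. For FAT and MRS only the U-test is prescribed. The missing half-tie term is a notation point and changes no calculation.

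**It is a reporting detail for exploratory analyses.** Their limited weight is accepted. However, the article does fix the measure for all the scores, so the point concerns a stated rule and not an omission. Nor would the results be uninterpretable: category counts could always be shown beside the estimate.

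**Conclusion.** The point holds conditionally. One effect measure is fixed for all secondary scores. If FAT and MRS have few grades and most patients change by 0 or 1, it will often give 0, with an interval including 0, beside a significant U-test. For moderate effects and complete data this is close to the rule. With mean imputation it is less extreme but still common, and with larger effects or wider change distributions it shrinks or disappears.

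The reach is limited to exploratory secondary analyses. Nothing here touches the primary test, the sample size, the significance levels or the stopping rule. It is a cheap improvement, best settled before the data are seen.

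**What to change.** In Statistical analysis, Secondary endpoints, add that for FAT and MRS, and for BI if its changes are heavily tied, P(X>Y) + ½P(X=Y) with its 95% CI is reported alongside the Hodges-Lehmann difference. This is the quantity that the U-test assesses. Optionally add the difference in the proportion improving by at least one grade with its 95% CI, using the method for proportions that the section already names. Keep Hodges-Lehmann as planned for the finer scales (WMFT, BBT, SIS, MAL). The half-tie term can be added to the written hypotheses for tidiness.

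Cost: one additional reported measure for two or three scales, a sentence of text and a line of code. No new data, patients or power are needed.

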#### Subgroups

In the subgroup analyses the results of the test inventories and assessments stated above are used.

#### Interim analyses

After half of the patients have concluded the rehabilitation program, an interim analysis will be performed. This will allow for an early termination of the study if the effects are greater than assumed for sample size determination while keeping an overall significance level of α = 0.05. The interim analysis is planned according to the designs suggested by Wang and Tsiatis
[34] and yields a nominal significance level of α1 = 0.01 for the interim analysis. At this time point, all three null hypotheses regarding the primary endpoint as stated above are tested at the full nominal significance level, and the study is terminated only if all null hypotheses are rejected.

For the final analysis, the three hypotheses of the primary endpoint are tested at a nominal significance level of α2 = 0.045 in the hierarchical manner described above. Specifically, the first hypothesis is tested at a significance level of α2(1) = 0.035. If this null hypothesis is not rejected, the second null hypothesis is tested at the remaining significance level of α2(2) = 0.01. However, if the first null hypothesis is rejected, the second is tested at the full nominal significance level of α2 = 0.045.

This procedure renders the following effects detectable in the different stages, as presented in Table
3. The effects are measured by the differences of medians, for which 95% confidence intervals (Hodges-Lehmann) are computed for both group comparisons.

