## Methods/design

### Trial design

The form of our clinical study will be: multicenter, open, randomized, placebo-controlled, paralleled group trial with three investigative arms conducted in Germany (5 sites). This study aims at demonstrating superiority of the videotherapy over both physical training and standardized physical therapeutic treatments. We will use equal number of patients for the randomization on the three groups (1:1:1).

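### The final-analysis fallback rule is valid but does not return unused alpha to the comparison with standard care; one sentence would recover a small amount of power at no cost to the 5% family-wise limit

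*Protocol article*

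**What the plan says.** The Trial design section gives the aim: "This study aims at demonstrating superiority of the videotherapy over both physical training and standardized physical therapeutic treatments". The Primary endpoint part of the statistical analysis lists two null hypotheses: H01 (videotherapy vs standard) and H02 (videotherapy vs non-video). They are tested in order with a split alpha, and "if the first hypothesis cannot be rejected, the second hypothesis can still be tested at the significance level" set aside for it.

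The Interim analyses section supplies the final-analysis levels:
- H01 receives 0.035.
- After a failure on H01, what is left for H02 is 0.01: "If this null hypothesis is not rejected, the second null hypothesis is tested at the remaining significance level".
- After a success on H01, H02 receives the whole 0.045: "if the first null hypothesis is rejected, the second is tested at the full nominal significance level of α2 = 0.045".

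Table 3 agrees. Its final row for video vs standard carries the single level 0.035, while the row for video vs non-video carries 0.01 or 0.045. Nowhere is H01 tested a second time.

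**The concern.** Alpha moves in one direction only. A success on H01 raises the level for H02 from 0.01 to 0.045, but a success on H02 at 0.01 does nothing for H01. Two mirror-image results are therefore treated differently:

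- p = 0.005 vs standard and p = 0.040 vs non-video: both hypotheses are rejected.
- p = 0.040 vs standard and p = 0.005 vs non-video: only H02 is rejected.

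In the second case one of the two superiority claims is lost, and it concerns the comparison on which the sample size rests. What is at stake is power for H01 and for showing both superiorities. Error control is not in question.

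**Working it through.** **Inputs from the protocol.** Final levels are 0.035, 0.01 and 0.045. The interim level is 0.01 at half the patients, with stopping only if all nulls are rejected. The sample size uses δ = 0.5, 90% power, 125 per group and 20% dropout, so 125 × 0.8 = 100 evaluable per arm.

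**Assumptions.** Change scores are normal, Mann–Whitney efficiency is 3/π ≈ 0.955, and the two comparisons share the videotherapy arm (correlation 0.5). Interim rejections count only if the trial stops. Effects other than 0.5 vs standard are illustrative.

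**1. The plan's own figures.** Noether's formula with P(X>Y) = Φ(0.5/√2), two-sided 0.035 and 90% power gives 100.3 completers per group; 100.3/0.8 = 125.4, against the stated 125. Power with 100 completers is 89.9% (Noether) or 91.1% (efficiency 3/π). Nominal levels 0.01 then 0.045, with correlation √0.5 between looks, give an overall alpha of 0.0498, against the stated 0.05. Both figures reproduce.

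**2. Why a retest is permitted.** Write the rule as a closed test:
- The intersection of H01 and H02 is rejected if p1 ≤ 0.035 or p2 ≤ 0.01 (0.035 + 0.01 = 0.045).
- Each single hypothesis may then be tested at 0.045, as the plan already does for H02.

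If p2 ≤ 0.01 the intersection is rejected, so H01 may be tested at 0.045. The result is weighted Holm with weights 0.035 and 0.01. It rejects everything the planned rule rejects, plus the cases with 0.035 < p1 ≤ 0.045 and p2 ≤ 0.01. The example falls there: 0.005 ≤ 0.01, then 0.040 ≤ 0.045.

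**3. Error rates, interim included.**

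| Truth | Planned rule | With retest |
|---|---|---|
| Both nulls true, any false rejection | 4.3% | 4.3% |
| Only H01 true (H02 clearly false) | 4.04% | 4.98% |
| Only H02 true (H01 clearly false) | 4.98% | 4.98% |

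The first row cannot change, because a retest happens only after H02 has already been rejected.

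**4. Ceiling on the gain at δ = 0.5.** The standardised effect is 0.5 × √(100 × 0.955/2) = 3.455. Power for H01 is Φ(3.455 − 2.108) = 0.911 at 0.035 and Φ(3.455 − 2.005) = 0.927 at 0.045. The retest can therefore add at most about 1.6 points, and less in practice because p2 ≤ 0.01 is also needed.

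**5. Simulated chance of showing both superiorities** (two-stage, 50 then 100 evaluable per arm; repeat runs agree to about 0.1 point).

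| Effect vs standard / vs non-video | Planned | With retest |
|---|---|---|
| 0.5 / 0.5 | 86.4% | 87.3% |
| 0.4 / 0.4 | 63.7% | 65.0% |
| 0.5 / 0.4 | 74.1% | 74.5% |
| 0.5 / 0.3 | 51.8% | 51.9% |
| 0.6 / 0.5 | 91.6% | 91.7% |
| 0.4 / 0.5 | 72.1% | 74.3% |
| 0.3 / 0.5 | 48.3% | 51.6% |

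At 0.5/0.5, power for H01 alone rises from about 91.2% to 92.1%.

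**The case against.** The strongest reply is that nothing here is wrong. The two analysis sections and Table 3 agree, the fallback procedure is pre-specified and controls the error rate, and the stated power for H01 is met. All of that stands.

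The reply on size also stands. The protocol puts H01 first because it expects the major difference there, and its Blinding section notes that more intense training may widen that difference. Non-video patients train too, whereas standard patients receive no trial treatment. The natural ordering is thus a larger effect against standard, where the gain is 0.1 to 0.4 points. The gains of 2 to 3 points, and the example p-values, belong to the reverse ordering.

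It is also fair that the retest has a price inside the 5% limit: when only H01 is true, a false claim against standard becomes about a quarter more likely (4.04% to 4.98%).

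Two further replies do not remove the point:
- If success means beating both controls, testing each at 0.045 would do and is slightly more powerful (87.6% against 87.3% at 0.5/0.5). That gives up a claim on one comparison alone, which the alpha split is built to allow and the retest preserves.
- The Interim analyses section speaks of three primary hypotheses. The Primary endpoint section and Table 3 list two, and the Secondary endpoints section makes non-video vs standard exploratory. The argument is for those two.

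A reader might infer that a trial with p = 0.040 and p = 0.005 simply fails, or that the rule is faulty. The documents do not support this. H02 has its own reserved level, so the result is a success on one comparison, and the rule keeps its promised error rate.

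**Conclusion.** The planned rule is valid but leaves some alpha idle: it never retests H01 at 0.045 after H02 is rejected at 0.01. The retest dominates it within the 5% family-wise limit. The benefit is about 0.9 points in the chance of showing both superiorities at effects 0.5/0.5, close to nil in the order the protocol expects, and 2 to 3 points only if the effect against standard is the smaller.

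These sizes rest on 100 evaluable patients per arm, normal change scores and the interim reading given above. If single interim rejections were instead kept without stopping, the error under both nulls would be about 5.5% with or without the retest, so the retest is not the cause of any excess there. This is an optional improvement. It is neither a flaw in error control nor a shortfall in the stated power.

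**What to change.** In the Primary endpoint and Interim analyses sections, add for the two primary hypotheses: *If H01 is not rejected at 0.035 but H02 is rejected at 0.01, H01 is retested at 0.045.* Name the procedure as weighted Holm with weights 0.035 and 0.01, and show 0.035 or 0.045 in the final video vs standard row of Table 3.

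The change needs no patients or data and keeps the family-wise limit. It must be written before unblinding, because a retest introduced after p = 0.040 has been seen would not be credible. The sponsor should accept knowingly that the error for H01 alone then uses the full 5% instead of about 4%. Keeping the present rule is also defensible.

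### The 95% Hodges-Lehmann intervals for the primary comparisons do not match the final test levels of 0.035, 0.045 or 0.01, so an interval can exclude zero when the null is not rejected

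*Protocol article*

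**What the plan says.** All references are to the protocol article, Statistical analysis.

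- **Test.** Under Primary endpoint: "The hypotheses will be tested using the exact *U*-test according to Mann and Whitney". Both alternatives are two-sided.
- **Overall level.** Under Interim analyses, the design is meant to allow early stopping "while keeping an overall significance level of α = 0.05".
- **Final level, videotherapy versus standard.** "the first hypothesis is tested at a significance level of α2(1) = 0.035".
- **Final level, videotherapy versus non-video.** If the first null stands, "the second null hypothesis is tested at the remaining significance level of α2(2) = 0.01". If it is rejected, "the second is tested at the full nominal significance level of α2 = 0.045". Table 3 repeats these levels.
- **Effect measure.** The same section closes with: "The effects are measured by the differences of medians, for which 95% confidence intervals (Hodges-Lehmann) are computed for both group comparisons".

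Nothing in the article adjusts the level of these intervals, calls them descriptive, or says how to read an interval that disagrees with its test. Under Secondary endpoints, 95% intervals accompany exploratory tests at 0.05, so there the two levels agree.

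**The concern.** The Hodges-Lehmann interval at level 1 − a consists of the shifts that a Mann-Whitney test at level a would not reject. A 95% interval therefore excludes zero when p < 0.05. At the final analysis the plan requires p below 0.035, 0.045 or 0.01. For any p between the assigned level and 0.05, the published interval points to an effect while the formal decision is non-rejection.

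What is at stake is interpretation. The interim look and the split of alpha exist to hold the overall error at 0.05. An unlabelled 95% interval on the primary effect offers a second, looser significance reading beside that scheme, and it matters most for borderline results. The conflict is between two levels that the article itself states, so it is not a detail left to a document that is not shown.

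**Working it through.** **Inputs from the article.** 125 patients per group with 20% dropout gives 125 × 0.8 = 100 evaluable per arm. Planning effect δ = 0.5 with 90% power at 0.035, two-sided (Sample size and Table 3).

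**Assumptions.** Normal approximation to the U-test, location shift, efficiency 3/π relative to the t-test. The two test statistics have correlation 0.5, because the equally sized arms share the videotherapy group. Final analysis only.

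**Reproducing the plan's figure.** n = 2 × ((z₀.₉₈₂₅ + z₀.₉₀)/0.5)² = 91.9 per arm. Dividing by 3/π gives 97, and dividing by 0.8 gives 122, against 125 stated. Power with 100 evaluable is 91.1%, against 90% stated. The approximation is close enough to the plan's own.

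**Each test alone.** The mean of the test statistic is δ × √(100 × (3/π)/2) = 6.91 δ, which is 2.07 at δ = 0.3 and 3.45 at δ = 0.5. The critical values are 1.960 (0.05), 2.005 (0.045), 2.108 (0.035) and 2.576 (0.01). The probability of a conflict is power at 0.05 minus power at the assigned level:

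| Test level | δ = 0 | δ = 0.3 | δ = 0.5 |
|---|---|---|---|
| 0.035 | 1.5% | 54.5 − 48.6 = 5.9% | 93.3 − 91.1 = 2.2% |
| 0.01 | 4.0% | 54.5 − 30.7 = 23.8% | 93.3 − 81.0 = 12.2% |
| 0.045 | 0.5% | 54.5 − 52.7 = 1.8% | 93.3 − 92.6 = 0.6% |

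(Differences were taken before rounding.) The 0.01 row is not a trial-level probability, because that level is used only when the first null is not rejected.

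**The whole final hierarchy.** I simulated both statistics jointly. The second test used 0.045 after a rejection and 0.01 otherwise. The chance of at least one conflict is first + second − both:

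| True effects | First interval | Second interval | Both | At least one |
|---|---|---|---|---|
| both 0 | 1.5% | 3.6% | 0.15% | about 5% |
| both 0.3 | 5.9% | 12.1% | 1.6% | about 16% |
| both 0.5 | 2.2% | 2.7% | 0.5% | about 4% |

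**Given that the 0.01 path is reached.**
- Both effects 0.3: the first null is not rejected in 51.4% of trials and a conflict on this path occurs in 11.2%, so 11.2/51.4 = about 22%.
- Both effects 0.5: 2.3% out of 8.9%, so about 26%.

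**An example.** Simulated data with 100 per arm and SD 5 (2.5 points ÷ 0.5) gave p = 0.0438 and an estimate of 1.50. The 95% interval is 0.04 to 2.88 and excludes zero. The null is not rejected at 0.035, and the 96.5% interval, −0.07 to 2.97, includes zero.

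**Width of matched intervals relative to 95%.** 2.108/1.960 = 1.08 for 96.5%, 2.005/1.960 = 1.02 for 95.5%, and 2.576/1.960 = 1.31 for 99%.

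**The case against.** The strongest reply is that no decision depends on the interval. Success and early stopping are defined only through U-tests at fixed levels, and the interval is introduced as an effect measure. Unadjusted 95% intervals beside adjusted tests are a common convention. This stands, and it limits the weight of the point. It does not remove it, because the article fixes both levels and does not say that the interval is descriptive.

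Three stronger readings are tempting, and the article does not support them.

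- **That conflict on the second comparison occurs in 24% or 12% of trials.** Those are the figures for a stand-alone test at 0.01. In the hierarchy that level applies only after the first null fails. At the planning effect of 0.5 for both comparisons, the second interval conflicts in about 2.7% of trials.
- **That the interim analysis has the same problem.** The article gives an interim level ("yields a nominal significance level of α1 = 0.01 for the interim analysis") but does not clearly plan interim intervals. The trial stops for efficacy only if all primary nulls are rejected at 0.01, and then every 95% interval also excludes zero.
- **That the effect measure is wrongly defined.** The Hodges-Lehmann estimate is the median of pairwise differences, which need not equal the difference of medians. But the method is named in the same sentence, so the estimator can be identified and this is a matter of terminology.

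**Conclusion.** The mismatch is real and minor. At the final analysis neither primary comparison is tested at the level that its 95% interval implies. The gap is trivial at 0.045, small at 0.035 and material at 0.01. Across the hierarchy, at least one interval contradicts its decision in about 16% of trials if both true effects are 0.3, about 4% if both are 0.5, and about 5% under the global null. Once the 0.01 path is reached, the second interval conflicts in about 22% (both 0.3) to 26% (both 0.5).

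A reader might infer that type I error is inflated or that the sample size is wrong. Neither follows, since decisions and error rates rest on the tests alone.

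The figures rest on 100 evaluable patients per arm, a normal approximation with 3/π efficiency, a pure location shift and correlation 0.5. They ignore selection by continuing past the interim. Ties in the WMFT scores could make the match between test and interval slightly inexact.

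**What to change.** In the closing sentence of Interim analyses, report the final-analysis intervals at the level tested: 96.5% for videotherapy versus standard, and 95.5% or 99% for videotherapy versus non-video according to whether the first null was rejected. Label any 95% interval that is kept as descriptive, unadjusted for the interim look and the split of alpha, and not to be read as a test.

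The cost is wording and somewhat wider intervals, with no change in sample size. There are two limits. The level of the second interval then depends on the result of the first test, which needs a sentence of explanation. And matching the nominal level aligns each interval with its test but is not a full group-sequential adjustment.
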